### Statistical Analyses

The statistical analysis is performed using the SPSS software package, version 22.0. The measurement data obeying the normal distribution are expressed as x ± s, and the *t-*test is used for comparison between groups. Non-normally distributed continuous variables are expressed as median with interquartile range and compared using the Mann-Whitney U test. The enumeration data are expressed by rate (%) and analyzed by the chi-square test or Fisher's exact test. *P* <0.05 is considered a significant statistical difference.

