### Sample Size

This is a prospective randomized controlled study. Patients meeting the inclusion and exclusion criteria are randomly divided into two groups, group A (AAF) and group B (EHF). Time to reach full enteral feeding is the primary outcome measure; the same research is unreported at present. According to Raimondi's study (15) and experience in clinical practice, the mean time to full enteral feeding in group A is 23.6 ± 15.6 days, accounting for a 30% disparity, the time to full enteral feeding between the two groups differs by approximately 7.08 days. Hypothesis tests are two-sided with a significance level of 5%, while the statistical power is set at 80%. In this study, Zα = 1.96, Zβ = 0.84, σ represents standard deviation, δ represents the difference between the mean values in the two groups, and the formula for calculating sample size is as follows:

$$\begin{array}{l} n=\frac{{\left(Z_{\alpha }+Z_{\beta }\right)}^{2}*2\sigma^{2}}{\delta^{2}} \end{array}$$

After calculation, a sample size of 76 per group is required, accounting for a 20% miss rate. Ninety-five patients per group need to be included, and the planned sample size of this study is at least 190 patients in total.

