### Randomization

Randomization will be performed using the SPSS software package (version 22.0) using a random number generator in a 1:1 ratio. A statistician who is not involved in recruitment and subsequent data analysis will generate the randomization list, and the list will be concealed. After random allocation lists have been generated, the allocation group (AAF or EHF) will be stored in sequentially numbered, sealed, opaque envelopes. These envelopes will be opened by a third-party individual at each study enrolment after baseline measures have been obtained.

The study will be double*-*blinded. A nutritionist who is not directly involved in inpatient care will prepare and label the formula with the participant's randomization number, date, and time of feeding, and then deliver the formula to the nurse caring for the infant. The medical and nursing teams caring for the infants will be unaware of the type of formula used for feeding. The trial statistician will perform data analysis and be kept unaware of treatment group assignment until the results are finalized.

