### Variables Studied

The investigator who is responsible for recruitment will perform all the evaluations and remain blinded to the status of the patients with regard to the intervention throughout the study.

Table 4 shows the demographic variables. The following variables: age, sex, birth weight, birth length, delivery mode, gestational age, multiple gestations, family history, birth history, and history of present condition.

**Table 4 T4:** Demographic variables.

**Variables**	**values**
Age Sex Gestational age Birth weight Delivery mode Multiple gestations Apgar score (1', 5', 10') Maternal health during pregnancy Adverse events at birth	Days Male/Female Weeks g vaginal delivery or cesarean section Yes/no 1-10

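### The primary comparison is unadjusted, although recorded gestational age and birth weight and a derivable age at randomisation could sharpen it; this is lost precision, not bias

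*Protocol article*

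**What the plan says.** All references are to the protocol article.

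- **Statistical Analyses.** For normally distributed data a t-"test is used for comparison between groups"; other continuous variables go to the Mann-Whitney U test. No covariate is named, and the primary outcome has no separate rule.
- **Randomization.** "Randomization will be performed using the SPSS software package (version 22.0) using a random number generator in a 1:1 ratio". Neither strata nor blocks are mentioned.
- **Variables Studied.** The baseline list includes "age, sex, birth weight, birth length, delivery mode, gestational age, multiple gestations". Table 4 gives age in days without a time point. Table 1 schedules weight, length and head circumference at baseline (T2) and at discharge (T5).
- **Primary Outcome.** Time to full feeds is indicated by the infant's age on the first day of full feeding, so the clock starts at birth.
- **Sample Size.** "the mean time to full enteral feeding in group A is 23.6 ± 15.6 days", and "the time to full enteral feeding between the two groups differs by approximately 7.08 days". On that basis "a sample size of 76 per group is required", raised to 95 per group for 20% loss.

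**The concern.** Infants are admitted within 24 hours of birth but randomised only once feeding intolerance has been diagnosed, after baseline measures are taken. The days before randomisation count in the primary outcome, yet the formula cannot influence them. They add variance that has nothing to do with treatment.

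Maturity is a second source of spread. Table 2 admits infants below 32 weeks or below 1,500 g with no lower limit on either, and the Background ties feeding intolerance to immaturity. The planning SD is wide: 15.6 / 23.6 = 0.66 of the mean.

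An unadjusted test leaves all of this in the error term. At stake are a wider confidence interval and lower power than the same infants could provide.

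**Working it through.** **Inputs from the Sample Size section.** "Hypothesis tests are two-sided with a significance level of 5" per cent; "the statistical power is set at 80" per cent; SD σ = 15.6 days; difference δ = 0.30 × 23.6 = 7.08 days; 76 evaluable per arm.

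**Step 1: the plan's own figure.** n = (1.96 + 0.84)² × 2 × 15.6² / 7.08² = 76.1 per arm, and 76 / 0.80 = 95. The stated size reproduces, apart from rounding 76.1 down. Power of the unadjusted t-test at 76 per arm is 79.4% (79.9% by the normal approximation).

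**Step 2: how much of the variance could be age at entry.** The document gives no SD for age at randomisation. If it were 5 or 7 days and independent of the later course (assumptions), its share of the planned variance would be 25 / 243.36 = 10% or 49 / 243.36 = 20%.

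**Step 3: power after adjustment, normal data.** In a linear model the residual SD is σ√(1 − R²). R² is assumed over a range. The power figures use the t distribution with δ = 7.08 and 76 per arm.

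| Assumed R² | Residual SD (days) | Power |
|---|---|---|
| 0 | 15.60 | 79% |
| 0.1 | 14.80 | 83% |
| 0.2 | 13.95 | 87% |
| 0.3 | 13.05 | 91% |
| 0.4 | 12.08 | 95% |

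**Step 4: price of the covariates.** With 152 infants, fitting three covariates inflates the variance of the treatment estimate by about 3 / (152 − 2 − 3 − 1) = 3/146 = 2%. The table leaves this out. Adjustment pays once R² exceeds about 0.02.

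**Step 5: skewed data.** With an SD two-thirds of the mean, time to full feeds may well be skewed. A simulation (3,000 runs per scenario, 76 per arm, three covariates) used log-normal days with mean 23.6 and SD 15.6 in one arm and values 1.3 times as large in the other. R² is on the log scale; the adjusted model is fitted to raw days.

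| R² | t-test | Mann-Whitney | Adjusted linear model |
|---|---|---|---|
| 0 | 70% | 75% | 69% |
| 0.2 | 68% | 72% | 76% |
| 0.4 | 68% | 74% | 84% |

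Power is lower throughout, largely because the SD rises with the mean in this scenario (1.3 × 15.6 = 20.3 in the second arm). The adjusted model on raw days gains about 3 points over Mann-Whitney at R² 0.2 and about 11 at R² 0.4. At R² 0 it falls below Mann-Whitney.

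**Step 6: validity of the planned tests.** In the same simulations, with normal and with log-normal data, type I error of the t-test and of Mann-Whitney stayed between 4.5% and 5.5%.

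**The case against.** The strongest reply is that nothing is broken. After randomisation an unadjusted comparison is valid, and the trial was sized for exactly this one. The infants' variability is already in the SD of 15.6. This stands, and it limits the point to efficiency.

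A reader might infer that, without stratification, a chance imbalance in maturity biases the result. The document does not support that. At 76 per arm a given covariate differs by 0.2 SD or more with probability of about 22%, but the standard error of the unadjusted test already allows for such imbalance. There is no bias on average and no excess of false positives. Nor does the article say that allocation is unrestricted; strata or blocks may be in a fuller protocol.

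The gain also rests on an R² that the document nowhere gives, and it could be small. How mixed the group is can be argued too: Table 2 restricts entry to infants appropriate for gestational age and excludes several serious conditions. Both points stand, which is why the range starts at R² 0. The power figures belong to a linear model for days and cannot be carried over to a Cox or competing-risks model.

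Finally, an adjusted analysis may sit in an analysis plan not shown. But the article is not silent on method: it states a rule for continuous outcomes, and that rule takes no covariates.

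**Conclusion.** The point holds as a recommendation about precision. The stated primary analysis ignores two recorded maturity variables and leaves pre-randomisation days in the error term. It is neither invalid nor underpowered on the plan's own assumptions.

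The size is conditional. With normal data the gain is about 4 points of power at R² 0.1, 8 at 0.2 and 15 at 0.4, less the roughly 2% variance cost. With skewed data it depends on the comparator and is modest against Mann-Whitney unless R² is well above 0.2. Some gain is likely because age at entry is part of the outcome by definition, but no figure in the document fixes how much. It would be too strong to call the adjustment free or to present any one row of the tables as the expected gain.

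**What to change.** Replace the t-test/Mann-Whitney rule for the primary outcome with one model, fixed before unblinding: linear regression (ANCOVA) of days to full feeding on treatment, gestational age, birth weight and age at randomisation. This keeps the mean difference in days on which the sample size rests. If the team expects skewness, specify log days instead, in advance. Keep the unadjusted test as a sensitivity analysis. Adjust weight, length and head circumference for their T2 values.

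Define age at randomisation explicitly as randomisation date minus birth date, since Table 4 does not say when age is taken.

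**Cost.** No added infants or visits, provided both dates are held. The statistical price is about 2% of variance for three covariates. If days are logged, the effect becomes a ratio of geometric means, and the sample size section should say how that relates to the 7.08-day difference.

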**Figure 1 F1:**
[figure not shown]
The overall design of the study.

**Table 1 T1:** Data collection schedule.

	**Staff member**	**T1**	**T2**	**T3**	**T4**	**T5**
Symptom of FI	Neonatal physician	**×**				
Informed consent	Research assistant	**×**				
Contact information	Research assistant	**×**				
Sex	Neonatal physician		**×**			
Gestational age	Neonatal physician		**×**			
Mode of delivery	Neonatal physician		**×**			
Apgar score	Neonatal physician		**×**			
Maternal issues	Neonatal physician		**×**			
Weight	Neonatal nurse		**×**			**×**
Gastric residual volume	Neonatal nurse			**×**	**×**	
Abdominal circumference	Neonatal nurse			**×**	**×**	
Length	Neonatal nurse		**×**			**×**
Head circumference	Neonatal nurse		**×**			**×**
Time to reach total enteral nutrition	Neonatal physician					**×**
Duration of abdominal distension	Neonatal physician					**×**
Duration of vomiting	Neonatal physician					**×**
Length of hospital stay	Neonatal physician					**×**
Cost of hospitalization						**×**
Time of parenteral nutrition	Neonatal physician					**×**
Main serum parameters	Neonatal physician			**×**	**×**	
Incidence of adverse events	Neonatal physician					**×**

*T1 screening; T2 baseline evaluation; T3 beginning of intervention; T4 end of intervention; T5 discharge*.

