#### Secondary Outcome

Duration of vomiting and abdominal distension (a 24-h abdominal circumference increase of ≥1.5 cm).Gastric residual volume (measured by aspirating with a 5-ml syringe before each feeding).Body weight, length, and head circumference during hospitalization.Length of hospital stay (days).Cost of hospitalization.Time (days) of parenteral nutrition.Change of abdomen circumference (measured at a specific time every day).Main serum parameters (blood, liver and kidney function, and electrolytes).Incidence of adverse events.

**Study endpoint**: The day of discharge

**Follow*-*up plan**: No.

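### Continuous secondary outcomes are assigned unadjusted two-sample tests although Table 1 collects an earlier value of the same variable; adjusting for it would usually give more precision at almost no cost

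*Protocol article*

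**What the plan says.** The Statistical Analyses section of the protocol article gives one rule for all continuous data. If the data are normal, the t "test is used for comparison between groups". If they are not, the rule is: "Non-normally distributed continuous variables are expressed as median with interquartile range and compared using the Mann-Whitney U test". The section names no covariate, analysis of covariance or regression model.

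The key to Table 1 reads: "T1 screening; T2 baseline evaluation; T3 beginning of intervention; T4 end of intervention; T5 discharge". The table marks these times for the variables at issue:

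- Weight, length and "Head circumference": T2 and T5.
- "Abdominal circumference", gastric residual volume and "Main serum parameters": T3 and T4.

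All six are secondary outcomes. Only one is defined as a change: "Change of abdomen circumference (measured at a specific time every day". Growth appears as "Body weight, length, and head circumference during hospitalization", with no statement of whether the final value or the change is compared. The same is left open for gastric residual volume and the serum parameters.

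**The concern.** When the same variable is measured before and after treatment, a two-sample test can take either the later value alone or the difference between the two. The first ignores the baseline. The second subtracts it with a fixed weight of one, whether or not that weight suits the data. A model that estimates the weight has a variance no larger than either, apart from the small price of estimating one slope.

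At stake is the precision of the growth, tolerance and serum comparisons. The Discussion itself raises the question of whether the two formulas meet preterm nutritional needs, and these are the outcomes that speak to it. The sample size was set for the primary outcome alone, so these comparisons have only whatever precision that number gives them.

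**Working it through.** **Inputs from the protocol article.** Sample Size: SD 15.6 days, difference 7.08 days, two-sided 5%, power 80%, 76 per group before loss, 95 after 20% loss. Randomization: 1:1. Table 1: measurement times as listed above.

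**Input not in the documents.** The correlation r between the earlier and later value. It is assumed over a range.

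**The plan's own figure.** n = (1.96 + 0.84)² × 2 × 15.6² / 7.08² = 76.1, stated as 76; 76 / 0.80 = 95 per group, 190 in total. The figure reproduces. It concerns the primary outcome and is used here only to fix n = 76 evaluable per group.

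**Variance of the treatment difference relative to raw final values, equal before and after SDs.**

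- Raw final value: 1
- Change score: 2(1 − r)
- Adjusted for own baseline: 1 − r²
- Adjusted relative to change score: (1 − r²) / [2(1 − r)] = (1 + r) / 2

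| r | change / raw | adjusted / raw | adjusted / change |
|---|---|---|---|
| 0.3 | 1.40 | 0.91 | 0.65 |
| 0.5 | 1.00 | 0.75 | 0.75 |
| 0.7 | 0.60 | 0.51 | 0.85 |

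**Cost of estimating the slope.** Factor 1 + 1/(2n − 4) = 1 + 1/148 = 1.0068, about 0.7%. With this included, adjusted / raw becomes 0.92, 0.76 and 0.51.

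**The same in power.** Take an effect that has 80% power on raw final values with 76 per group. With relative variance f, power is Φ(2.80/√f − 1.96). At r = 0.3, 0.5 and 0.7, change scores give 66%, 80% and 95%; the adjusted analysis, slope cost included, gives 83%, 90% and 97%.

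**Unequal SDs.** Let k = SD(before) / SD(after). Change-score variance relative to raw is 1 + k² − 2rk. Subtracting 1 − r² leaves (k − r)². The excess is never negative, but it is zero when k = r. Example: r = 0.5, k = 0.5 gives 1 + 0.25 − 0.50 = 0.75 for the change score and 1 − 0.25 = 0.75 for the adjusted value, so there is no gain.

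**Low r.** At r = 0.1, adjusted / raw is 0.99 × 1.0068 = 0.997, in effect no gain. At r = 0 it is 1.0068, a loss of 0.7%.

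**Are the earlier values true baselines?** For T2, yes: Randomization says the allocation envelope is opened only after baseline measures are obtained. For T3, Table 1 says only that it is the start of the intervention. It does not say whether the measurement precedes the first study feed.

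**The case against.** The strongest case against is that nothing here is an error. An unadjusted two-sample test is valid under 1:1 randomisation, the section is a short general summary that ties no test to a named outcome, and covariates for secondary outcomes are often left to an analysis plan, which is not shown. Validity stands in full. The appeal to a missing plan stands only in part, because the article does not stay silent: it names the tests, and none of them uses the baseline.

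Three stronger readings are tempting, and the documents do not support them.

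- *A reader might infer that a change score over-corrects whenever r is below 1.* That is so only with equal SDs. In general it over-corrects only when r is below k. The documents give neither quantity, and infants grow between T2 and T5, so equal SDs cannot be taken for granted for the growth measures.
- *A reader might infer that chance baseline differences will be taken for formula effects.* The error rate of a valid test already allows for chance imbalance. What is lost is precision.
- *A reader might infer that every one of these outcomes is planned as a raw final value or a single before-after change.* Only abdominal circumference is defined as a change, and it is measured daily; gastric residual volume is measured before each feed. A single pair of values may not be the quantity compared.

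Two further limits stand. Discharge falls at a different time for each infant, which may weaken the T2 to T5 correlation and so the gain for growth; adjustment does not resolve that timing problem. And a plain linear model would not by itself suit the skewed variables for which the article reserves Mann-Whitney U.

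**Conclusion.** The point holds as a minor, inexpensive improvement to a stated analysis. The named tests leave collected baseline information unused. The likely benefit is a variance reduction of about 9% to 49% against raw final values, and 35% to 15% against change scores, as r goes from 0.3 to 0.7. These figures rest on an assumed r and on equal before and after SDs. Outside those assumptions the gain over change scores can fall to zero, and with r near 0 there is none over raw values. For the T3 variables the point also depends on those values preceding the first study feed. The unadjusted tests remain valid, and the primary comparison and the 190 infants are not in question.

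**What to change.** Add to Statistical Analyses that each continuous secondary outcome with a baseline is analysed by a linear model. The final value is the outcome; arm and that variable's own T2 or T3 value are the covariates; the adjusted difference is reported with its 95% confidence interval. This covers weight, length, head circumference, abdominal circumference, gastric residual volume and the serum parameters. For clearly skewed variables, specify a log transformation or a rank-based analysis of covariance. State whether T3 values are taken before the first study feed, and use them as baseline only where they are. For the outcomes now left open, state which quantity is compared.

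The cost is a few sentences and one degree of freedom per model, about 0.7% of variance at 76 per group. No new data are needed, as Table 1 already schedules them. The wording should be fixed before any unblinded comparison. How to handle differing discharge times for the T5 measures remains a separate matter.

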### Recruitment

First, persons in charge of recruitment and quality control are identified. Patients who met all inclusion criteria and none of the exclusion criteria are recruited in this study through the electronic medical record system. Then, their legal guardians are informed of the content of this study, written informed consent is signed, and a registration form is filled. The quality controller randomly chooses from guardians of patients over the course of recruitment and asks if they have read and understood the written informed consent form, to ensure that the rights of patients and guardians are safeguarded.

### Data Collection and Management

Data management and monitoring will be performed by using the ResMan Research Manager (http://www.medresman.org), and all data sets will be password protected. Only the investigators directly involved with the study will have access to the account number and password. Investigators correctly, completely, clearly, and timely record data in the case report forms (CRFs) according to original observation. The CRFs after inspection need to be transmitted to the data administrator of the clinical research in time. Data will be entered into the ResMan by the authorized researchers. Data entry will be by double entry, and matching will be conducted after inconsistent data has been reviewed. Original CRFs are stored in numerical order and kept in locked cabinets after the completion of data entry and review.

## Discussion

This randomized, prospective, clinical trial aims to assess the effects of AAF or EHF on improving FI. A total of 190 preterm infants with FI are included and randomly divided into two groups: the AAF-fed and EHF-fed groups. Time to reach full enteral feedings, duration of vomiting, abdominal distension and gastric residual volume, and other indicators are evaluated.

The mechanisms by which AAF improves feeding intolerance remain incompletely unclear. AAF is composed of free amino acids, no lactose, and a higher percentage of medium chain triglycerides. The amino acids are essential for intestinal function and have an important role in mucosal blood perfusion, growth, and immunity (20). AAF may promote gastric emptying, decrease the duration of parenteral nutrition, and reduce the risk of nosocomial infections and parenteral nutrition-associated complications.

However, there have been some concerns as to whether AAF and EHF meet the nutritional needs of preterm infants (16, 21). In this study, the patients with FI are fed AAF or EHF for a short term; once the clinical presentation of FI improved, HM or PF are switched back. Jang et al. (16) reported that the patients with FI who fed AAF for a short term showed improvement in the symptoms and signs of FI with proper body weight gain, and did not develop any adverse clinical signs or symptoms during AAF feeding. There was not any disadvantage in preterm infants on growth between the EHF-fed group and the PF-fed group in the long-term (12 weeks) study (22), and long-term treatment with AAF was safe and allowed adequate body growth (23).

The study also has some limitations that should be noted. Due to the imperfect follow-up system, the lack of post-intervention follow*-*up makes it difficult to judge long*-*term prognosis. Additionally, the study population are low birth weight preterm infants with a high risk for FI, who are not representative of the entire neonatal population, and therefore, the findings may not be generalizable to other populations. Furthermore, the study formulas differ not only in the protein equivalent component (free amino acids vs. extensively hydrolyzed protein), but also in other aspects (such as nutrient density, osmolarity, and minerals). These differences may potentially contribute to the differences in results. The study design does not permit us to elaborate on the different effects of each of these differences separately.

The large sample size is one of the greatest strengths of this study, the successful implementation of our study will provide robust evidence for formula alternatives in preterm infants with FI. This may further improve feeding intolerance and outcomes of preterm infants.

